### Recruitment and consent process

Participants will be identified by trained clinical staff on admission to the rehabilitation hospital, based on the eligibility criteria outlined in table 1. If patients express an interest in the study, a participant information sheet will be given to them along with the contact information of the research team should they have any questions. Interested and eligible participants will be approached by a study team member and asked to provide written informed consent (>24 hours after receiving the participant information sheet and receiving a full verbal explanation of the study). If participants are unable to provide a signature due to their injury, a witness will be present to sign confirming the prospective participant’s verbal consent.

**Table 1 T1:** Participant inclusion and exclusion criteria

Inclusion criteria	Exclusion criteria
For patients: At least 18 years old Males and females Have had an SCI* (AIS A, B, C or D) between C5 and T12 levels within 12 months; injuries graded AIS D on consent must be using a wheelchair >75% of the time for mobility Are cleared by their medical team to begin standard of care rehabilitation. Can move their shoulders and arms voluntarily to operate the arm-crank ergometer. Compliance: understands and is willing, able and likely to comply with all study procedures and restrictions. Consent demonstrates an understanding of the study and willingness to participate, as evidenced by voluntary written informed consent. For healthcare providers/staff: Currently be a member of the medical team supporting subacute spinal cord injured patients at MCSI. Be at least 18 years old. Be involved in the clinical care/rehabilitation of patients (eg, clinician, occupational therapist or physical therapist)	Pregnant (women who become pregnant will be advised to notify clinical staff, and on notification, will be withdrawn from the trial) Under the age of 18 years. Have an SCI lower than the T12 neurological level. Have an SCI above the C5 neurological level, intubation, a tracheostomy in situ or requires mechanical ventilation. Medical complications or premorbidities from the injury that, in the opinion of the healthcare or research team, would restrict or prevent the participation in exercise rehabilitation, pose undue personal risk or introduce bias into the trial. Co-occurring traumatic brain injury or cognitive impairment that either impacts the ability to follow study instructions and/or provide informed consent. Unable to provide fully informed consent.

* Spinal Cord Injury Levels & Classification.

AIS, American Spinal Injury Association (ASIA) Impairment Scale; C, cervical; MCSI, Midland Centre for Spinal Injuries; SCI, spinal cord injury; T, thoracic.

### Eligibility criteria

#### Randomisation

After preintervention assessments (A1 and A2), recruited participants will be randomly allocated into one of the two study groups using a computer-generated randomiser. Figure 1 provides an overview of the trial flow, illustrating the sequence of assessments, randomisation and subsequent testing. The A1 and A2 assessments are conducted prior to randomisation to gather initial data on participants to understand initial status and variability among participants. Conducting randomisation after these assessments minimises the risk of allocation bias, which could occur if knowledge of group assignment influenced initial measurements. Randomisation will be performed by an independent researcher ([name]) not involved in the recruitment process to minimise selection bias. Block randomisation methods will be used to ensure balance in group sizes. In consultation with the Director of Statistics and Research Strategy at the Birmingham Clinical Trials Unit, it was determined that any imbalances of the participants recruited to the study would be down to chance. Each participant will be assigned a unique participant identification number and the corresponding trial group will be provided according to the list. Blinding is not achievable during data collection, therefore, neither participants nor data collectors will be blinded. However, to minimise bias, data analysts will be blinded to participant allocation.

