Reduced mobility as a result of both injury-related functional impairments and the need for medical stabilisation post-SCI can cause the cardiovascular system to undergo immediate alterations in its function as it adjusts to the new reduced metabolic demands.^14^ In as little as 6 weeks after injury, peripheral arteries in the paralysed lower limbs can undergo remodelling, resulting in reduced flow and diameter of the femoral artery.^15^ This remodelling is in conjunction with the diminished sympathetic tonic activity to the blood vessels below the lesion,^16^ which can result in profound hypotension. Moreover, individuals with higher-level injuries (ie, cervical and upper-thoracic injuries above the sixth thoracic level (≥T6)), often experience more pronounced hypotension due to potentially disrupted autonomic pathways.^17 18^ Beyond the acute pathological issues associated with blood pressure (BP) variability,^19^ chronic exposure to unstable BP has been shown to detrimentally impact cardiac and vascular structure and function,^6 20^ which can be measured via ultrasound. Assessing the autonomic regulation of the cardiovascular system non-invasively can be achieved using heart rate variability (HRV).^21^ Specifically, the frequency domain of HRV predicts cardiovascular dysfunction in individuals with SCI.^22^

SCI significantly contributes to obesity by altering fat-free mass and causing physical impairments such as paralysis or paresis, which restricts energy expenditure associated with movement, thereby increasing cardiometabolic risk.^23^ Such changes disrupt metabolic homeostasis,^24 25^ resulting in disorders such as insulin resistance and dyslipidaemia, which in turn increases the risk of developing type 2 diabetes mellitus and CVD in individuals with SCI.^26^ Individuals with both traumatic and non-traumatic SCI experience an elevated risk of CVD, highlighting the importance of routine CVD risk screening during rehabilitation for both groups.^27^

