### Arm cycle ergometry training

ACET will be performed on an arm cycle ergometer (Monark 881E, Monark Exercise AB, Vansbro, Sweden) against individually determined levels of resistance. This initial exercise intensity will be prescribed as a power output that corresponds to ~55% and ~62% of each participant’s V̇O_2peak_ for individuals with paraplegia and tetraplegia, respectively, determined from their baseline graded cardiopulmonary exercise test (CPET). These population-specific values have been chosen as recent research indicates they more closely correspond to moderate-intensity exercise classifications than utilising non-disabled guidelines.^72^ This protocol can be successfully implemented in individuals with higher-level cervical SCI by using tensor bandages over Activehands grip aids to secure the participants’ hands to the ergometer.^73^ The height of the ergometer will also be positioned so that the crank apex will be at or lower than the height of the participants’ shoulders. Participants can self-select their arm-cycling cadence, but >70 revolutions per minute will be recommended.

Participants in the ACET group will initially perform 3×30 min per week of moderate-intensity arm-crank exercise, in keeping with SCI-specific exercise guidelines to improve cardiometabolic health.^74^ Participants will be allowed breaks in each exercise bout as required. By the end of the first week, participants should be able to cycle continuously for 30 min. At 4 and 7 weeks, the opportunity to perform an additional exercise session will be given to the participant, so that during weeks 7–10 of the intervention participants, could be performing 5×30 min per week of moderate-intensity ACET (figure 2). Such a gradual progression in exercise volume has been advocated in the Exercise and Sports Science Australia position statement on exercise and SCI,^75^ and ensures participants are achieving exercise guidelines promoted by reputable health authorities for the general population (eg, ~150 min of moderate-intensity exercise per week).^76^

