### Statistical analysis

The Shapiro-Wilk test will be used to test the distribution of the continuous variables for demographic and outcome measures. Continuous variables will be reported as mean±SD for normally distributed data or median with IQRs for non-normally distributed data; categorical variables will be reported as frequency. Specific injury characteristics will be considered for subanalysis (ie, injury level, injury severity). A two-way repeated measures analysis of variance (ANOVA) will be applied to examine the main effects of the group/time and group–time interaction. Post hoc analyses will be conducted where significant group-time interaction effects are identified. Significance level will be set at 0.05 for all statistical tests. Standardised effect sizes (Cohen *d*) will also be calculated and interpreted based on the following criteria: small (*d*=0.2), medium (*d*=0.5) and large (*d*=0.8) effects.^128^

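### The primary model for cfPWV does not adjust for injury level, which the protocol ties to cardiovascular status and training; a prespecified covariate would protect against chance imbalance at almost no cost

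*Protocol article*

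**What the plan says.** **Randomisation.** The Randomisation section of the protocol article states: "Block randomisation methods will be used to ensure balance in group sizes". It names no stratification or minimisation factor. After consulting the clinical trials unit, the authors conclude that "any imbalances of the participants recruited to the study would be down to chance".

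**Analysis.** The Statistical analysis section names the model: "A two-way repeated measures analysis of variance (ANOVA) will be applied to examine the main effects" of group and time and their interaction. It names no covariate. Injury level has one role there: "Specific injury characteristics will be considered for subanalysis (ie, injury level, injury severity").

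**Injury level elsewhere in the article.**
- Table 1 admits injuries "between C5 and T12 levels within 12 months", AIS A to D, so tetraplegia and paraplegia are mixed.
- The Background says that people with injuries at or above T6 "often experience more pronounced hypotension due to potentially disrupted autonomic pathways". It adds that long exposure to unstable blood pressure harms cardiac and vascular structure and function, and that dysfunction at these levels limits exercise energy expenditure.
- The Arm cycle ergometry training section sets starting intensity at about 55% and 62% of peak oxygen uptake "for individuals with paraplegia and tetraplegia, respectively". Progression follows target heart rate in paraplegia and perceived exertion in cervical injury.

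**The concern.** That an imbalance arises by chance is true of every randomised trial. It guarantees validity on average, but it does not make a given imbalance harmless in a trial with 32 evaluable participants. The article gives its own reasons to think that vascular change over ten weeks might depend on injury level. Neither the allocation nor the named model uses that information, and results split by injury level leave the main estimate as it was.

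Two things are at stake. If one arm happens to contain more higher-level injuries, and cfPWV changes differently in them, the estimated effect in this trial moves by the product of the two. And whatever variance in change is due to injury level stays in the error term.

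**Working it through.** **1. The plan's own figure.** Power calculation and sample size gives 16 per group, 95% power, 5% significance and a difference of 1 m/s. The figure of 32 cannot be reproduced, because no SD, standardised effect or within-person correlation is stated. I therefore solved for the SD of change that it implies, treating the interaction as a two-sided comparison of change between two groups:
- normal approximation: SD = 1 / [(1.960 + 1.645) × √(2/16)] = 0.78 m/s
- noncentral t, 30 df: SD = 0.76 m/s (standardised effect 1.32; variance 0.576)

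**2. Probability of imbalance.** The share of higher-level injuries is not stated; I assume roughly 30% to 60%. With K such participants split at random into two arms of n, the number in one arm is hypergeometric and the imbalance is |2k − K| / n. Because |2k − K| is odd or even with K, the probability jumps between neighbouring values of K, so a range is more honest than one figure.

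| Arms | K | P(at least 20 points) | P(at least 25 points) |
|---|---|---|---|
| 21 v 21 | 12 | 8.6% | 8.6% |
| 21 v 21 | 13 | 18.1% | 4.3% |
| 21 v 21 | 20 or 22 | 12.2% | 12.2% |
| 21 v 21 | 21 | 21.7% | 6.3% |
| 16 v 16 | 10 | 25.2% | 25.2% |
| 16 v 16 | 11 | 13.5% | 13.5% |
| 16 v 16 | 15 or 17 | 15.6% | 15.6% |
| 16 v 16 | 16 | 28.9% | 28.9% |

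Over the assumed range, 20 points or more occurs in about 9% to 22% of trials at 21 v 21 and 14% to 29% at 16 v 16. The second row of figures assumes that loss to follow-up is unrelated to injury level.

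**3. Shift in the estimate.** Shift = imbalance × difference in mean cfPWV change between injury levels. The article gives no such difference; I take 0.25 to 1.0 m/s as an assumption.

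| Difference in change | 20 points | 25 points |
|---|---|---|
| 0.25 m/s | 0.05 | 0.06 |
| 0.5 m/s | 0.10 | 0.13 |
| 1.0 m/s | 0.20 | 0.25 |

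So the shift is 5% to 25% of the 1 m/s target. Larger differences hardly fit the plan: with equal shares, 1.5 m/s would account for 0.25 × 1.5² / 0.576 = 98% of the implied variance of change.

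**4. Precision.** With equal shares, injury level explains 0.25 × g² / 0.576 of the variance of change, where g is the difference between levels. At 16 per group:

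| g | Variance explained | Residual SD | Power after adjustment |
|---|---|---|---|
| 0.25 m/s | 2.7% | 0.75 | 95.5% |
| 0.5 m/s | 10.8% | 0.72 | 96.8% |
| 1.0 m/s | 43.4% | 0.57 | 99.8% |

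The power before adjustment is 95% by construction. Spending one degree of freedom on the covariate (29 in place of 30) leaves these figures the same to one decimal.

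**5. Type I error of the unadjusted comparison (simulated, 16 per group).** Averaged over randomisations it is about 5% for all three values of g. Given a realised split of 10 v 6 higher-level injuries (25 points), it is about 5.3%, 6% and 8% for g = 0.25, 0.5 and 1.0 m/s. With a perfectly balanced split it falls below 5%, which is why the average holds.

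**The case against.** The case for leaving the plan alone has real strength.

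- **The contrast is one of change.** cfPWV is measured at A1 and A2, before randomisation, and the trial is powered on the interaction. Stable differences in cfPWV between injury levels cancel. This stands: only a difference in change can move the estimate, and the article does not state that there is one.
- **Intensity is individualised so that all train at moderate intensity.** This stands as far as it goes. It tends to even out relative load, so differing prescriptions are not evidence of differing cfPWV response.
- **Unstratified randomisation is valid and was chosen on trials-unit advice.** This stands, and nothing below asks for it to be changed.
- **Covariates are usually settled in a statistical analysis plan, which is not shown.** This stands in part. An unseen plan may adjust. But the article is not silent: it names the model and gives injury level another role, so an adjusted primary analysis would depart from the published text.

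A reader might go further and infer that a large imbalance is likely, that injury level is the main determinant of cfPWV, or that the result will be biased. The documents support none of these. The probabilities above stay below 30%, and 25 points or more at 21 v 21 has a probability of only 4% to 12%. The article presents higher injury level as a contributor, in hedged terms. And randomisation keeps the unadjusted comparison unbiased on average.

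**Conclusion.** The concern holds as a point about efficiency and about protecting one small trial against an unlucky allocation. The protocol gives its own grounds for treating injury level as prognostic, then names a primary model that ignores it and relies on a subanalysis that cannot adjust the main result.

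The likely gain is modest: 0.5 to 1.8 points of power if change differs by 0.25 to 0.5 m/s between levels, and more (95% to 99.8%) only if the difference reaches 1.0 m/s. Without adjustment, an imbalance of 20 to 25 points would put 0.05 to 0.25 m/s of the estimate down to case mix. The conclusion that adjustment is worth having does not depend on these values, because it costs almost nothing if they prove smaller. Their size rests on three assumptions that the article does not supply: the share of higher-level injuries, the difference in change between levels, and an SD of change inferred from the stated power.

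**What to change.** Leave the randomisation list as it is. In the analysis plan, replace the unadjusted ANOVA as the primary test with a comparison of cfPWV at A3 between groups by ANCOVA, or an equivalent mixed model. Use two covariates: cfPWV at A2, and injury level in one prespecified split (for example cervical v thoracic, or at or above T6 v below) taken from the neurological classification done at screening. Fix the split before any data are seen by allocation. Use the same approach for the secondary cardiovascular outcomes, with their own A2 value where one exists. The subanalysis by injury level can stay as exploratory, and A1 can still describe variability before the intervention.

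The cost is one line of wording and one degree of freedom per covariate: with 32 evaluable participants, 28 residual degrees of freedom (32 − 4) in place of 30 (32 − 2). No new data are needed, and no clinical procedure changes.

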**Figure 1 F1:**
[figure not shown]
Trial flow chart. CON group, control group receiving standard of care in the rehabilitation setting; ACET group, intervention group undergoing arm crank ergometry training in addition to standard of care. ACET, arm-crank exercise training.

### Patient and public involvement

Patients and community-dwelling individuals with SCI were not formally involved in the development of the trial (ie, formulating the research questions, design of the study or the selection of outcome measures). A patient with SCI reviewed the study protocol and provided a letter of support prior to the submission of the grant application. Further, participants will complete a standardised questionnaire regarding the acceptability and feasibility of the exercise intervention, described in detail in the Feasibility section below. Four open-ended questions will explore facilitators, barriers, benefits and suggestions for future exercise programmes at the subacute stage of SCI. Members of the study team are actively engaged with the wider SCI community and have experience with designing and conducting exercise interventions in this population.^66^,^68^

### Standard of care

After newly acquired SCI, patients are transferred from local trauma centres to one of the 11 specialised SCI centres in the UK, such as RJAH. Care at these centres adheres to established guidelines and best practices,^69 70^ providing patients with multidisciplinary support from a team of healthcare professionals. This team typically includes consultants (senior physicians), physiotherapists (to improve mobility and strength), occupational therapists (to improve independence in daily activities), dietitians and social workers.

The standard of care rehabilitation programme encompasses a broad range of services designed to address the physical, psychological and social needs of inpatients. Important aspects include the introduction to wheelchairs and adaptive aids, psychological support and education on self-care, such as skin integrity, bowel and bladder management and recognising potential complications. Patients have a minimum of 15 hours of rehabilitation per week, including appointments with a multidisciplinary team of clinicians and specialists, goal planning and case conferences.^70^ Additionally, the programme offers training for caregivers and family members, alongside tailored guidance on returning to work or exploring new opportunities, as appropriate.

Initially, postinjury and on admission, general strategies for preventing complications from spinal instability or neurological compromise are a priority. Skin integrity and bladder and bowel care are essential areas of focus for healthcare professionals, with no specific focus on addressing cardiovascular health per se. Currently, inpatient rehabilitation programmes aim to promote independence and facilitate optimal reintegration into the community.^71^

### Arm cycle ergometry training

ACET will be performed on an arm cycle ergometer (Monark 881E, Monark Exercise AB, Vansbro, Sweden) against individually determined levels of resistance. This initial exercise intensity will be prescribed as a power output that corresponds to ~55% and ~62% of each participant’s V̇O_2peak_ for individuals with paraplegia and tetraplegia, respectively, determined from their baseline graded cardiopulmonary exercise test (CPET). These population-specific values have been chosen as recent research indicates they more closely correspond to moderate-intensity exercise classifications than utilising non-disabled guidelines.^72^ This protocol can be successfully implemented in individuals with higher-level cervical SCI by using tensor bandages over Activehands grip aids to secure the participants’ hands to the ergometer.^73^ The height of the ergometer will also be positioned so that the crank apex will be at or lower than the height of the participants’ shoulders. Participants can self-select their arm-cycling cadence, but >70 revolutions per minute will be recommended.

Participants in the ACET group will initially perform 3×30 min per week of moderate-intensity arm-crank exercise, in keeping with SCI-specific exercise guidelines to improve cardiometabolic health.^74^ Participants will be allowed breaks in each exercise bout as required. By the end of the first week, participants should be able to cycle continuously for 30 min. At 4 and 7 weeks, the opportunity to perform an additional exercise session will be given to the participant, so that during weeks 7–10 of the intervention participants, could be performing 5×30 min per week of moderate-intensity ACET (figure 2). Such a gradual progression in exercise volume has been advocated in the Exercise and Sports Science Australia position statement on exercise and SCI,^75^ and ensures participants are achieving exercise guidelines promoted by reputable health authorities for the general population (eg, ~150 min of moderate-intensity exercise per week).^76^

**Figure 2 F2:**
[figure not shown]
Adherence infographic. ACET, arm-crank exercise training.

For participants who choose not to perform the additional exercise sessions at 4 and 7 weeks, their decision will be respected and they will continue with the prescribed 3×30 min per week of ACET as outlined in the protocol, which is still in line with the minimal SCI-specific volume of exercise to improve cardiometabolic health.^74^ We will document the reasons for non-participation in the additional exercise sessions to inform future studies tailored to the SCI population. This approach allows us to identify the volume of aerobic exercise that is realistically achievable in the inpatient setting, and consequently, the individualised nature of the arm-crank exercise prescription enables us to determine what exercise training load is broadly achievable for patients with subacute SCI.

Should participants be discharged during the 10-week intervention period, they will receive an arm-crank ergometer (the same model during inpatient care) for continuing the intervention in their own homes for the remainder of the 10-week intervention. A member of the study team will visit the participant’s home to ensure proper setup of the device and supervise the first home-based session to ensure the correct exercise intensity is adhered to. Participants will wear a chest-worn HR monitor (Polar H10, Kempele, Finland), which will be paired to and stored on the cloud-based Polar Beat app (Polar, Kempele, Finland) via a commercial tablet (iPad, Apple, Cupertino, California, USA), while maintaining completed training logs for all arm-crank exercise sessions. Participants will receive a weekly phone call from a member of the study team to ensure compliance. This pragmatic approach has been used in another exercise trial performed with patients with SCI in the subacute setting,^77^ and considers the variability in injury rehabilitation duration (which depends on injury characteristics and medical complications) to ensure patients can complete the 10-week intervention. Exercise intensity progression will be regulated during the 10-week intervention for participants with paraplegia by adjusting the resistance during each session to achieve a target heart rate corresponding to moderate-intensity for each participant. Central (ie, overall effort and fatigue, accounting for the entire body’s sensation of exertion) and peripheral (ie, focused on localised sensations of effort and fatigue in the shoulders and arms) rating of perceived exertion (RPE) will be captured at the end of each exercise session, with RPE’s of 12–13 or 14–17 on a 6–20 Borg Scale corresponding to moderate or vigorous-intensity exercise, respectively.^72^ For participants with cervical injuries, if self-reported RPE is <12 the resistance for the subsequent exercise session will be increased to ensure an element of progressive overload is delivered, following consultation with the chief investigator (CI), who is an accredited clinical exercise physiologist ([name]; [name]). Perceptual regulation of exercise intensity using RPE has been shown to be a valid approach in the SCI population.^78^

During the first 4 weeks of the intervention, a research team member will adopt a flexible approach to scheduling supervised sessions, accommodating participant needs. The team member will assist with the physical setup for the arm-crank exercise, as well as provide verbal encouragement and guidance regarding exercise performance. In line with the consensus-based recommendations for exercise research in SCI,^64^ behaviour change techniques such as goal setting and planning with participants to set exercise goals during the session, using exercise logs to help participants track their progress, offering regular, constructive feedback during their exercise sessions and celebration of milestones (eg, completing a session with no breaks) will be implemented. BP will be monitored where individuals report symptoms of low or high BP (eg, light-headedness or headache) before or after exercise sessions during this initial 4-week period. At the start of week 5, participants will begin to transition to autonomous training with the goal to being fully autonomous by the end of week 6. During the transition period, the research team will provide only minimal guidance; for example, when participants struggle to remember proper setup or execution. This ensures that participants can independently perform exercise sessions over weekends when the weekly exercise session frequency increases towards the latter stages of the intervention. The transition from assisted exercise sessions to autonomous training reflects the principles of the self-determination theory,^79^ particularly in the context of autonomy and competence. Participants will be gradually given more control and responsibility over their exercise sessions to foster autonomy. As participants gain confidence and proficiency, the lessened reliance on external assistance promotes a sense of competence in their ability to exercise.

Adherence will be periodically assessed every 3 weeks to determine the feasibility of the participant achieving the minimal amount of exercise sessions during the 10-week period. This pragmatic approach accounts for the associated complexities of working with this population in the subacute setting that may result in exercise sessions being missed. Participants will be given the option to catch up with missed exercise sessions during subsequent weeks. If a participant misses a period of 3 weeks’ worth of consecutive exercise sessions (n=9) and is unable to compensate after review with a member of the study team, then they will be withdrawn from the trial due to non-compliance (figure 2).

